## Abstract

**Background:**

The prevalence of common mental disorders increases in humanitarian emergencies while access to services to address them decreases. Problem Management Plus (PM+) is a brief five-session trans-diagnostic psychological WHO intervention employing empirically supported strategies that can be delivered by non-specialist lay-providers under specialist supervision to adults impaired by distress. Two recent randomized controlled trials in Pakistan and Kenya demonstrated the efficacy of *individually* delivered PM+. To make PM+ more scalable and acceptable in different contexts, it is important to develop a *group version* as well, with 6–8 participants in session. A study is needed to demonstrate the feasibility and acceptability of both the intervention in a new cultural context and the procedures to evaluate Group PM+ in a cluster randomized controlled trial.

**Methods:**

This protocol describes a feasibility trial to Group PM+ in Sindhuli, Nepal. This study will evaluate procedures for a cluster randomized controlled trial (c-RCT) with Village Development Committees (VDCs), which are the second smallest unit of government administration, as the unit of randomization. Adults with high levels of psychological distress and functional impairment will receive either Group PM+ (*n* = 60) or enhanced usual care (EUC; *n* = 60). Psychological distress, functional impairment, depression symptoms, posttraumatic stress disorder (PTSD) symptoms, and perceived problems will be measured during screening, pre-treatment baseline, and 7–10 days after the intervention. Qualitative data will be collected from beneficiaries, their families, local stakeholders, and staff to support quantitative data and to identify themes reporting that those involved and/or effected by Group PM+ perceived it as being acceptable, feasible, and useful. The primary objective of this trial is to evaluate the acceptability and feasibility of the intervention; to identify issues around implementation of local adaptation methods, training, supervision, and outcomes measures; and to assure that procedures are adequate for a subsequent effectiveness c-RCT.

**Discussion:**

Outcomes from this trial will contribute to optimizing feasibility and acceptability through cultural adaptation and contextualization of the intervention as well as refining the design for a c-RCT, which will evaluate the effectiveness of Group PM+ in Nepal.

**Trial registration:**

ClinicalTrials.gov identifier: NCT03359486

## Background

Humanitarian crises, such as the earthquake in Nepal in April 2015, cause significant psychological and social suffering. Nepal’s fragmented and under-resourced mental health and social services are not able to cope with such a high level of need [1]. The country has 0.22 psychiatrists and 0.06 psychologists per 100,000 people, mainly working in large cities [1]. Nepal has basic health care units with primary care staff and midwives, and in most districts, there are other community care providers, often working for NGOs. The availability of this system makes a model of care provision through non-specialists a particularly important implementation strategy.

In low-resource settings, mental health interventions may need to be short of duration and carried out by non-specialists in the communities to make them sustainable and feasible to implement on a broader scale. A simplified psychological intervention, *Problem Management Plus* (*PM+*), has been developed by the World Health Organization (WHO) to address this. It has four core features that make the intervention suitable for low-resource settings exposed to adversities: a brief intervention (five sessions) (1) delivered individually or in groups; (2) delivered by non-specialists (high school graduates with no mental health experience), using the principle of task shifting; (3) designed as a trans-diagnostic intervention, addressing a range of client-identified emotional (e.g., depression, anxiety, stress) and practical problems; and (4) designed for people in communities in low- and middle-income countries (LMIC) affected by any kind of adversity (e.g., violence, disasters) [2].

Recent randomized controlled trials (RCTs) in Peshawar (Pakistan) and Nairobi (Kenya) have indicated individually delivered PM+ to be effective in diminishing depression and anxiety symptoms, managing self-selected practical or psychological problems, and improving daily functioning [3, 4]. The first evaluation of a Group PM+ is underway in Pakistan [4]. This paper describes the study protocol of a feasibility trial with Group PM+ in Nepal before evaluating effectiveness in a fully powered cluster RCT (c-RCT) [5]. Feasibility studies are valuable to address issues related to process, resources, management, or scientific approaches [6, 7] in so the issues can be addressed before conducting definitive randomized trials.

### Objectives

For Group PM+ in Nepal, we will implement trial procedures to gather information about feasibility, acceptability, safety, and delivery of the intervention in a Nepali community setting, and to assess training, supervision, and outcomes measures. The Group PM+ manual has been adapted for post-earthquake rural Nepal through qualitative formative research (has not been published). The feasibility trial will further identify whether the clinical and content adaptations are appropriate for the setting. Possible problems of acceptability, compliance, delivery of the intervention, randomization, blinding, recruitment, and retention will be assessed before the effectiveness c-RCT is conducted [7]. The feasibility study will include two trial arms: enhanced usual care (EUC) and Group PM+. We will assess the acceptability and feasibility of the Group PM+ intervention compared to EUC and will collect data for the design of a full-scale effectiveness c-RCT of Group PM+ compared to EUC. We will use a mixed-methods design with qualitative and quantitative approaches to determine feasibility. The objectives include the following:To evaluate the feasibility and acceptability of the Group PM+ intervention in a rural Nepal community [primary objective];To evaluate the feasibility and acceptability of intervention delivery by Group PM+ trained non-specialists;To determine recruitment and retention rates for Group PM+ sessions;To assess feasibility and acceptability of outcome measures;To assess feasibility of cluster randomization procedure to limit biases and risk of contamination;To assess ethics and safety of trial procedures using the adverse event protocol.

## Methods/Design

### Setting

Nepal is a low-income country in South Asia with a population of approximately 27 million with the majority (83%) of the population living in rural areas [8]. The country suffered a decade-long civil war from 1996 to 2006 with a range of psychiatric sequelae among adults and children [9–11]. In 2015, there were two major earthquakes in 2015, killing approximately 10,000 people and injuring 20,000. A mental health epidemiological study in Sindhupalchowk, Gorkha, and Kathmandu conducted 3 months post-earthquake found that one in three adults were experiencing depression and anxiety, one in five adults engaged in harmful alcohol use, and one in ten adults had current suicidality [12]. The compromised infrastructure and limited availability of specialized mental health services is an impediment to addressing this burden of mental health problems.

The study will take place in Sindhuli district, a region southeast of Kathmandu, which was heavily impacted by the earthquakes. In Sindhuli, 250 people were injured and 15 were killed. Over 22,000 households were fully damaged and 10,000 partially damaged. In response to the earthquake’s effects on Sindhuli, Transcultural Psychosocial Organization (TPO) Nepal in collaboration with International Medical Corps (IMC) conducted mental health and psychosocial support (MHPSS) activities in over half of the district’s Village Development Committee (VDCs) from 2015 to 2017. TPO Nepal is a Nepali non-governmental mental health research and training organization, with specific expertise in humanitarian settings [13]. For the Group PM+ feasibility study, two Village Development Committees (VDCs) that had not previously received services were selected for randomization to either EUC or the intervention. Approximately 5000 people live in each VDC.

The selected VDCs have a diverse population with over 15 ethnicities, including Brahman/Chhetri, Magar, Tamang, and Dunwar. The national language Nepali is spoken by the majority of inhabitants. A formative qualitative study in these VDCs demonstrated that residents of these VDCs have minimal access to and awareness of mental health issues and its treatment. Each VDC has one government health post, which represents the first and most accessible portal of care, though often not the well-resourced. Primary healthcare workers in these facilities include health assistants, community medical assistants, auxiliary nurse midwives, and female community health volunteers (FCHVs).

### Design

Randomization will occur at the VDC level, and one VDC will receive the intervention while the other will receive EUC. Though not identical, the two VDCs are similar in population size, ethnic demographics, and access to health facilities. The two VDCs will be randomized in a public drawing by the District Public Health Officer (additional details provided below in the *Randomization* procedure). The two VDCs are separated by an adjoining VDC in attempt to limit intervention contamination among the beneficiary populations. Because there are two units of analysis for this trial, adjustment for clustering will be considered for analyzing the effectiveness of the definitive trial.

### Intervention: EUC versus Group PM+ intervention

Until recently, treatment-as-usual in rural Nepal for individuals with common mental disorders (CMD) in Nepal usually consists of no psychological/psychiatric treatment in local health facilities. Whereas experiencing a CMD rarely leads to treatment initiation, persons with severe mental illnesses are typically brought by family members to tertiary psychiatric services in the Kathmandu valley, and this is often after a long delay between onset of symptoms [1]. Beginning in 2012, the WHO mental health Gap Action Programme (mhGAP) Intervention Guide was adapted for use in Nepal and piloted in Chitwan district through the Programme for Improving Mental Health Care (PRIME) [14]. After the 2015 earthquakes, the mhGAP Humanitarian Intervention Guide [15] was adapted and contextualized for Nepal, and Nepali psychiatrists were taught to train primary care workers using mhGAP. This approach was used in Sindhuli. Therefore, the EUC arm in Nepal will receive a referral to primary care-based depression treatment.

Participants in the Group PM+ arm will receive five 3-h sessions of Group PM+. Each session focuses on teaching participants’ techniques to manage their stressors and problems. These sessions include (1) managing stress, (2) behavioral activation, (3) managing problems, (4) strengthening social support, and (5) review of techniques [16]. See Table 1 for more details on each session.

**Table 1 Tab1:** Mechanisms of action of Group PM+ intervention

PM+ mechanisms of action	Description of mechanism	Implementation of mechanism
Stress management	Participants learn deep breathing. They are encouraged to incorporate this mechanism into daily life (i.e., when doing housework, walking, etc.). Grounding techniques are incorporated to bring participants back to the present.	Session 1
Behavioral activation	Participants review the inactivity cycle. They choose a small activity that they enjoy doing (i.e., making and drinking tea, meeting a friend, etc.) and create a detailed plan about when and how to conduct this activity as a first step in breaking the inactivity cycle.	Session 2
Managing problems	Participants learn which of their problems are solvable and which are unsolvable. One problem is chosen among the solvable problems, and participants brainstorm tangible solutions, then creating manageable steps to accomplish their goals.	Session 3
Strengthening social support	Participants learn to recognize who among their family and friends are existing and potential sources of support and how best to strengthen connections with them. Social network mapping activities are incorporated in this mechanism.	Session 4

Note: The first four sessions of PM+ each addresses a specific mechanism of action. The fifth and last session is a review of the mechanisms of actions learned in the previous sessions

There will be a total of 60 participants in each arm. In the intervention arm, there will be approximately 7–10 groups with six to eight participants per group, separated by gender and with gender-matched facilitators. Facilitators will be supported by volunteer helpers in organizing the logistics of the group sessions, reminding participants about the sessions, and meeting non-attenders (participants who do not show up for Group PM+ sessions). Participants will be provided with calendars and reminder calls by the facilitators’ helpers, if necessary, to decrease dropout rates.

To conduct awareness-raising activities and facilitate recruitment, five non-specialists will be recruited in the EUC arm and another five in the Group PM+ arm. The requirement for the non-specialists will be at least 10 years of education, over 25 years of age, and living in either the EUC or Group PM+ VDC. The non-specialists will be trained by TPO Nepal for 20 days on basic psychological skills to become community psychosocial workers (CPSWs). Twenty days is the standard length for CPSW training through TPO Nepal, based on the expectation that briefer training would not equip facilitators to provide quality care to intervention participants. CPSWs from the intervention arm will then be given a 10-day Group PM+ training using the adapted manual and other clinical materials. Intervention training includes education on adversity and its impact upon mental health, basic counseling skills, delivering Group PM+, skills in group facilitation, and facilitator self-care. Group “Helpers” will receive a basic 2-day training on assisting facilitators during Group PM+ sessions and participating alongside CPSWs in practice PM+ groups. The main role of helpers will be logistics and child care. Competency and fidelity will be assessed with modified version of the Enhancing Assessment of Common Therapeutic Factors (ENACT) tool tailored for Group PM+ [17].

### Feasibility criteria

The primary objective is to evaluate feasibility and acceptability of both the intervention and the trial procedures for the subsequent c-RCT through the collection of both quantitative and qualitative data [4]. Because feasibility and acceptability are complex domains, both quantitative and qualitative indicators will clarify what procedures to carry on to the full trial and where modifications should be made to study design or content [18]. The following quantitative indicators will determine progression to the main trial:*Fidelity to Group PM+ elements at the level of 75% or greater* according to the mean fidelity checklist for Group PM+ elements across all sessions;*Lack of significant socio-demographic group differences*; tabulation of descriptive summaries for baseline characteristics comparing Group PM+ participants and EUC participants without significant group differences in education, economic status, age, gender, and medical comorbidities;*Retention of at least 67% of participants* through completion of five Group PM+ sessions;*Fewer than 15% missing items* on outcome measures across all assessments;*Presence of adverse events among fewer than 10%* of participants and any serious adverse events;

The following qualitative indicators will determine progression to the main trial:*Identification of qualitative themes* reporting that both CPSWs and beneficiaries perceive Group PM+ as being acceptable, feasible, and useful; the qualitative data will be coded for themes that participation reduces psychological distress, that participation does not damage familial or community relations, that participation is perceived as safe, and that participation is not perceived as stressful resulting in worsening mental health (see Table 2);

**Table 2 Tab2:** Qualitative domains and objectives

Domains	Participants interviewed	Sample research questions
1. Acceptability of Group PM+	Participants, family, CPSWs, community, psychosocial team	Is PM+ stigmatizing? Is it acceptable for CPSW to deliver PM+? What were parts of the program that could have been changed to make the program more acceptable for the community?
2. Implementation logistics; PM+ sites, local leadership	CPSWs, community, RAs and research staff, psychosocial team	How would we enhance project implementation (in terms of venue, coordination with local leadership, etc.)?
3. Feasibility of PM+ and burden (time, frequency, distance for providers and participants)	Participants, family, CPSWs, community, psychosocial team	How would make this program more sustainable? How would make this program more effective? Should the program be longer?
4. Fidelity and supervision (areas of deviation and cause, competency, amount and form of supervision)	CPSWs, psychosocial team	How did the CPSWs deviate from the material in the PM+ manual? Why did they deviate from the material? Was there a need for more or less supervision? What were the challenges to supervision?
5. Utility (perceived benefit) of PM+	Participants, family, CPSWs, community, psychosocial team	How do CPSWs perceive participant experience? What problems is PM+ helpful for? What problems is PM+ not helpful for? Who is PM+ useful for?
6. Contagion	Participants (control group), family, CPSWs, RAs and research staff, psychosocial team	Did anyone involved in PM+ teach friends, family, and community members PM+ techniques? Did the mechanisms of action for PM+ reach the control VDC? If so, how did those in the control group learn?
7. Blinding/randomization; sources and timing of unbinding	CPSWs, mhGAP, community, RAs and research staff, psychosocial team	When did RAs and CPSWs know that different groups received different treatment? How did they know about the different groups?
8. Recruitment and retention (participants and providers)	Participants, family, CPSWs, community, RAs and research staff, psychosocial team	What were challenges to recruitment? What were challenges to retention of participants in the program? What are possible solutions to recruitment and retention?
9. Adverse events, ethics, safety	Participants, family, CPSWs, mhGAP, RAs and research staff, psychosocial team	Were staff equipped to handle any adverse events? What was the type and fBMW80481requency of adverse events referred?
10. Referral and control condition	Participants, family, CPSWs, mhGAP, community, psychosocial team	Were mhGAP services available? Was medication available in local health posts? Was the TPO counselor used by the community? Was transportation to local referrals available to those who needed it?
11. Assessment feasibility, acceptability, interpretation	Participants, RAs and research staff, CPSW	Were the assessments feasible to conduct? Did the participants understand the assessments? What were the challenges to conducting assessments?

Feasibility and acceptability will be evaluated by these indicators to determine progression to the full trial. In domains where criteria are met, we will retain the procedure for the full trial. In domains where criteria are not met, we will modify procedures for the full trial. The presence of any adverse events and serious adverse events will be addressed by the trial team to identify alternative strategies for the full trial and Data Safety Monitoring Committee, which is described in detail below. The number of feasibility and acceptability criteria that are not met will determine the extent of intervention and trial design modification.

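### The baseline criterion rests on significance tests between two single VDCs, so neither passing nor failing it says whether the cluster randomization or the recruitment worked

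*Protocol article*

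**What the plan says.** The Feasibility criteria section opens its list of five numerical indicators with "The following quantitative indicators will determine progression to the main trial". The second indicator calls for descriptive baseline summaries of the Group PM+ and enhanced usual care (EUC) participants, to be found "without significant group differences in education, economic status, age, gender, and medical comorbidities". It gives no alpha, no test, no size of difference that matters and no rule for multiple comparisons.

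The same section attaches consequences. Where a criterion is met, the procedure is kept. Otherwise, "In domains where criteria are not met, we will modify procedures for the full trial". The number of unmet criteria sets how far the design is revised.

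The Design section says that "one VDC will receive the intervention while the other will receive EUC". On the two places chosen it says: "Though not identical, the two VDCs are similar in population size, ethnic demographics, and access to health facilities". On clustering it says only that "adjustment for clustering will be considered for analyzing the effectiveness of the definitive trial". The intervention section gives the size: "There will be a total of 60 participants in each arm".

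**The concern.** This is the only one of the five quantitative indicators that compares the arms at baseline. It therefore carries much of the quantitative weight for the objective of assessing whether cluster randomization limits bias. With one VDC per arm, a participant-level test answers a different question, namely whether two villages differ in who was enrolled. Villages ordinarily differ somewhat, whether or not the draw was sound.

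There are two possible errors. If the criterion is missed, the team may change a procedure that worked. If it is met, the team keeps a procedure on the strength of a test that could easily have missed a material imbalance.

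The test also cannot isolate the more plausible threat. Under Recruitment, the VDC is already allocated when candidates attend the family meeting. Only those in the Group PM+ arm hear about the intervention there, and they then decide whether to enrol. Selection at that step would look the same in the baseline table as a pre-existing village difference.

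**Working it through.** The protocol gives no failure probability, alpha or ICC for this criterion, so there is no stated figure to reproduce.

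**Inputs from the protocol.** One VDC per arm (Design); 60 participants per arm (intervention section); five characteristics: "education, economic status, age, gender, and medical comorbidities" (Feasibility criteria).

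**Assumptions.** Two-sided alpha 0.05 for each variable; participant-level tests that ignore VDC; five independent variables; ICC from 0 to 0.05.

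**1. Is a valid test available?** Two VDCs in two arms leave 2 − 2 = 0 degrees of freedom for between-VDC variance. That variance cannot be estimated from these data, so no analysis plan could supply a test that allows for clustering.

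**2. Chance that a correctly run draw misses the criterion.**

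- Design effect: DE = 1 + (60 − 1) × ICC
- Error per test: p = 2 × [1 − Φ(1.96/√DE)]
- At least one of five significant: 1 − (1 − p)^5

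| ICC | DE | 1.96/√DE | p per test | any of five |
|---|---|---|---|---|
| 0 | 1.00 | 1.960 | 5% | 23% |
| 0.01 | 1.59 | 1.554 | 12% | 47% |
| 0.02 | 2.18 | 1.327 | 18% | 64% |
| 0.05 | 3.95 | 0.986 | 32% | 86% |

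**3. Sensitivity.** A slightly different inflation factor, 1 + 60 × ICC/(1 − ICC), sets the true variance against the within-VDC variance that a naive test would use. It gives 22.6%, 47.8%, 64.9% and 87.1% for the same ICCs, and passes 50% at an ICC of about 0.011. With that factor:

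- pairwise correlation 0.5 between the variables gives 18%, 39%, 55% and 80%;
- alpha 0.01 with independent variables gives 5%, 19%, 36% and 69%.

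**4. What a pass leaves open, ignoring clustering.**

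- Smallest significant difference in means: t(0.975, 118) × √(2/60) = 1.980 × 0.1826 = 0.36 SD.
- Smallest significant difference in proportions near 50%: 1.96 × √(2 × 0.25/60) = 0.179, about 18 percentage points.
- Power for a true gap of 0.3 SD: the noncentrality is 0.3/0.1826 = 1.64, which gives 37%.
- Power for 50% against 40%: 19%.

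**The case against.** Several points on the other side have force.

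- **Failure is not a stop.** A reader might infer from the opening of the criteria list that a significant difference blocks the main trial. The same section says that procedures are modified, the Discussion repeats this, and no stop rule is stated. This point stands.
- **Usual failure is not established.** A reader might infer that the criterion will usually fail by chance. That needs an ICC, an alpha and independence that the protocol does not give. It is untrue at ICC 0 to 0.01 with alpha 0.05, and at ICC up to 0.02 with alpha 0.01. Two well-matched VDCs would lower the rate further. This point stands.
- **Some of the failures are real differences.** At ICC 0.05 the two VDC means truly differ with an SD of √(2 × 0.05) = 0.32. Many of the significant results at the higher ICCs would therefore detect real village differences. They are false alarms only if read as evidence against the randomization procedure. This point stands and limits how the percentages may be read.
- **Looking at baseline differences is legitimate.** Because enrolment follows allocation, imbalance is a relevant signal, though an imperfect one. This is a reason to keep the comparison in descriptive form.
- **The test may be defined in an unseen analysis plan, and the protocol says that inference testing is limited.** Alpha and the choice of test could well be defined there. The confounding of arm with VDC could not be removed there, and the criterion as written turns on significance. This point does not rescue the rule.

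**Conclusion.** The criterion is a badly chosen decision rule. Two parts of that conclusion need no assumed ICC. With one VDC per arm, a significant result cannot be attributed to the draw, to recruitment or to ordinary village differences. With 60 per arm, a non-significant result is compatible with observed gaps of up to about 0.36 SD, or about 18 percentage points near 50%; these limits take alpha as 0.05.

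The failure rates of 23% to 86% are conditional on ICC 0 to 0.05, two-sided alpha 0.05 and independent variables. They are lower with correlated variables, a smaller alpha or closely matched VDCs. Even with no clustering at all, five independent tests at 0.05 would flag a sound draw nearly one time in four.

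The consequence is an uninformative trigger for keeping or changing procedures. This is an external feasibility study, no data pass to the full trial, and the criterion is read beside four other quantitative indicators and the qualitative ones. The priority is moderate.

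**What to change.** Remove the significance wording from the second indicator. Keep the planned tabulation, present it by VDC, and report standardized differences without p-values. Use the characteristics that differ most, descriptively, to choose stratification or restricted-randomization variables for the full cluster trial.

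If an indicator about the procedure itself is wanted, base it on conduct: whether the draw was carried out as described, and whether recruitment in each VDC followed the plan. Include the proportion of people screening positive who enrol after the family meeting, compared by arm, because that bears directly on recruitment after allocation.

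The cost is the rewording of one criterion. No new data are needed: the baseline table is already planned, and the study flowchart already follows recruitment in both VDCs.
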